# AUtomated Risk Assessment for Stroke in Atrial Fibrillation (AURAS-AF) - an automated software system to promote anticoagulation and reduce stroke risk: study protocol for a cluster randomised controlled trial

**DOI:** 10.1186/1745-6215-14-385

**Published:** 2013-11-13

**Keywords:** Stroke, Atrial fibrillation, Prevention, Reminder systems, Anticoagulants, Primary care, Electronic medical records

## Abstract

**Background:**

Patients with atrial fibrillation (AF) are at significantly increased risk of stroke. Oral anticoagulants (OACs) substantially reduce this risk, with gains seen across the spectrum of baseline risk. Despite the benefit to patients, OAC prescribing remains suboptimal in the United Kingdom (UK). We will investigate whether an automated software system, operating within primary care electronic medical records, can improve the management of AF by identifying patients eligible for OAC therapy and increasing uptake of this treatment.

**Methods/Design:**

We will conduct a cluster randomised controlled trial, involving general practices using the Egton Medical Information Systems (EMIS) Web clinical system. We will randomise practices to use an electronic software tool or to continue with usual care. The tool will a) produce (and continually refresh) a list of patients with AF who are eligible for OAC therapy - practices will invite these patients to discuss therapy at the start of the trial - and b) generate electronic screen reminders in the medical records of those eligible, appearing throughout the trial. The software will run for 6 months in 23 intervention practices. A total of 23 control practices will manage their AF register in line with the usual care offered. The primary outcome is change in proportion of eligible patients with AF who have been prescribed OAC therapy after six months. Secondary outcomes are incidence of stroke, transient ischaemic attack, other major thromboembolism, major haemorrhage and reports of inappropriate OAC prescribing in the data collection sample - those deemed eligible for OACs. We will conduct a process evaluation in parallel with the randomised trial. We will use qualitative methods to examine patient and practitioner views of the intervention and its impact on primary care practice, including its time implications.

**Discussion:**

AURAS-AF will investigate whether a simple intervention, using electronic primary care records, can improve OAC uptake in a high risk group for stroke. Given previous concerns about safety, especially surrounding inappropriate prescribing, we will also examine whether electronic reminders safely impact care in this clinical area.

**Trial registration:**

http://ISRCTN 55722437

## Background

Despite improving trends in incidence, stroke remains a major health burden in the United Kingdom (UK), and internationally. Cerebrovascular disease is still the second largest cause of mortality in England and Wales [1], and has a greater disabling impact than any other chronic disease [2]. Improved management of risk factors has been central to recent improvements in outcomes [3], but a notable exception is the management of stroke risk in patients with atrial fibrillation (AF).

AF is a major independent risk factor for stoke, conveying up to a five-fold increased risk [4]. AF-associated strokes are generally more severe, with greater case fatality and subsequent disability than those not associated with AF [5]. Anticoagulation is established as an effective method of reducing stroke risk (by up to 67%) in patients with AF [6,7]. Despite the evidence of benefit, however, there remains considerable underuse. Recent studies place UK prescribing at as low as 53 percent of those eligible (based on national clinical guidelines of the time) [8], with up to 34 percent not prescribed and without a recorded contraindication or refusal [9]. This underuse is also evident internationally [10,11]. A number of factors contribute to this, including clinician misconceptions over risk of haemorrhage, especially in older people; time implications of the management of the most commonly used anticoagulant, warfarin; and confusion over eligibility [12]. There are risks from anticoagulation, notably haemorrhage, and some patients at high risk of bleeding should be excluded from this treatment. The pros and cons of anticoagulation are, however, often misjudged by clinicians, and based on the balance between haemorrhage and thromboembolism risk, most should be considered for OACs [13].

Decision support tools have been highlighted as one option to promote evidence-based prescribing of anticoagulants in AF [14]. Patient-specific electronically generated reminders - those which draw on routine medical record data to generate reminders specific to a patient - produce moderate, but significant, improvements in clinical processes, including prescribing [15]. However, concerns remain over their use, including the appropriateness of discussing issues outside the patient’s agenda during a consultation (resulting in a loss of patient autonomy) [16]; their impact on consultation length and flow [17]; and clinicians developing a reliance on them [18]. In the case of OAC therapy in AF, there is an added risk that an important decision might be rushed in the opportunistic setting.

We aim to develop an intervention to promote oral anticoagulation in eligible patients with AF (defined by the National Institute for Health and Clinical Excellence (NICE) guidance TA249 [19]), and further to test its effectiveness and safety. We do not differentiate between types of OAC (for example the most commonly used warfarin, or newer OACs such as dabigatran). Our intervention builds on the approach of the existing GRASP-AF tool [9] (drawing on routinely collected primary care data to identify eligible individuals with AF for OAC), but in addition will automatically update itself by repeatedly interrogating the practice database, and will be linked to screen reminders. Our intervention follows the established principle of repeated, electronically embedded audit cycles in primary care, typified by the UK Quality and Outcomes Framework (QOF) that supports the care of the more common chronic diseases [20]. Critically, to our knowledge, no such tool has been previously assessed in a randomised trial in this area of care.

### Aim

The aim of this trial is to investigate the impact of an automated system to identify patients with AF who are eligible for oral anticoagulant therapy (defined by NICE guidance TA249 [19]) to reduce stroke risk and to identify barriers to commencing recommended care using the tool.

### Objectives

The objectives of this trial are as follows:

1. To examine whether an automated software system operating within electronic medical records to identify patients with AF who are eligible for oral anticoagulant therapy will increase uptake.

2. To investigate whether the electronic software system can produce short term reductions in thromboembolism in high risk patients with AF.

3. To examine the safety of the electronic software system in promoting anticoagulation in patients with AF, including its impact on inappropriate prescribing and haemorrhages.

4. To examine patient and practitioner views of electronic systems that incorporate automated reminders in primary care and their impact on the primary care consultation and practice.

5. To investigate barriers and enablers to the successful uptake of an electronic audit and reminder tool to promote anticoagulation in patients with AF by primary care teams.

6. To explore reasons why patients with AF are not prescribed anticoagulants and identify any barriers to recommended prescribing that persist after the use of an electronic audit and reminder system.

## Methods/Design

### Study design

We will use a cluster randomised controlled trial (Figure 1) to investigate whether a decision support tool in electronic primary care records safely increases anticoagulant prescribing in eligible patients with AF. The general practice is the unit of allocation and study participant because the intervention aims to improve prescribing at a practice level. The intervention phase will last for 6 months, with data collection immediately following, and after a further 6 months. Control practices will undergo pre-/post-assessment, but will not receive the active software tool. We shall conduct a 3-month pilot study before the main phase, and a process evaluation in parallel with it.

**Figure 1 F1:**
[figure not shown]
**Outline design of the AURAS-AF trial.** AF = Atrial Fibrillation; GP = General Practitioner.

### Study setting and population

The study is set in English general practices, situated within the South East of England, Central England, and East Midland and South Yorkshire Primary Care Research Networks (PCRNs), which use the EMIS Web clinical system. We exclude practices that have carried out a major audit of anticoagulant prescribing (including the systematic invitation of patients) within the last 2 years; those previously involved in research into anticoagulation (including those involved in the pilot study) or those who have begun using the EMIS Web system within the last 3 months. EMIS are the largest among several providers of clinical software to UK general practice and their Web version is becoming widely adopted across the UK. Study practices will be recruited through a letter of invitation sent from the study team, through the local PCRN, with a practice guardian providing consent [21,22]. All practices using EMIS Web within the study region will be given equal opportunity to participate in the study.

### Intervention

The intervention is an electronic software tool installed in practice clinical systems. The tool identifies patients with AF who are eligible for anticoagulants based on recent guidelines (NICE TA249) [19], and are not currently prescribed therapy. We have designed the tool to operate in the EMIS Web clinical system. The tool will identify eligibility by interrogating data held in patient medical records. The NICE TA249 eligibility criteria are operationalised using the relevant clinical codes (see Additional file 1). Given that some criteria defining eligibility (see below) may be poorly coded, the tool highlights (through screen messages) patients with suspected relevant diagnoses (diabetes, heart failure, or hypertension), based on other aspects of their medical record (detailed decision rules available from the authors). These must be addressed by the clinician, with the diagnosis either confirmed or rejected, before proceeding. For instance, in current practice, most patients with known, symptomatic heart failure will be on the QOF Heart Failure register, a register that requires echocardiographic evidence of reduced left ventricular ejection fraction or a diagnosis of heart failure by a cardiologist. It is very unlikely that a patient will be on this register if they have neither NYHA class 2 symptoms (or greater) nor echocardiographic evidence of a low ejection fraction. However, in cases not on the register but where clinical codes suggest they should be, this will be questioned using automatically generated screen messages. Similar decision rules apply to possible uncoded diabetes and hypertension. In addition, the tool requests clarification over the nature (thromboembolic or haemorrhagic) of past recorded strokes, where non-specific electronic codes have been applied to the record. This is important as the distinction has a very important influence on eligibility for OAC therapy. This clarification is obtained by responses to screen prompts and these responses will be collected during the study.

The tool has two components:

1. A search module that maintains a list of patients diagnosed with AF, highlighting the group eligible for anticoagulation under current recommendations and who are currently not prescribed OAC therapy. According to NICE TA249 [19] patients are considered eligible if they meet one or more of the following criteria:

••previous stroke, transient ischaemic attack or systemic embolism

••left ventricular ejection fraction below 40%

••symptomatic heart failure of New York Heart Association (NYHA) class 2 or above

••age 75 years or older

••age 65 years or older with one of the following: diabetes mellitus, coronary artery disease or hypertension.

Once activated, the software will automatically refresh the list every 24 hours using data in the electronic medical records.

2. It will generate onscreen reminders, prompting clinicians (either general practitioners or practice nurses) about the need for anticoagulation in patients with AF. Screen reminder messages will appear whenever the electronic record of a patient eligible for, but not currently being prescribed anticoagulants, is opened by a clinician. These reminders must be actively responded to, with the clinician choosing from a number of options as indicated below. Options 1 and 2 will remove the screen message, but it will return next time the record is opened; options 3 and 4 will remove the screen message, which will not reappear as long as the corresponding ‘Read’ code is entered into the record or an OAC is prescribed respectively; option 5 permanently stops reminders.

The wording of the reminder is as follows:

This patient with Atrial Fibrillation is at raised risk of stroke. Anticoagulation is recommended unless contraindicated.

Please indicate your intended management:

1. I am not a clinician able to initiate anticoagulant therapy.

2. We do not have time to decide during this consultation over starting anticoagulation.

3. The patient is already taking anticoagulation, so no action needed, but I will apply the code ‘Anticoagulation monitoring’ to stop further alerts appearing.

4. We intend to start anticoagulation.

5. We have decided not to start anticoagulation because (tick all that apply):

* Evidence of atrial fibrillation (or history of it) is absent/inconclusive

* Patient preference (after benefits have been explained & risks discussed)

* Concern over on-going risk of serious haemorrhage

* Other reason/s (which I am recording in the notes)

Note - changes may be made to wording before the main phase, dependent on pilot results.

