### Control practices

Control practices will continue with usual care, which as of April 2012 included requirements placed on practices by the Quality and Outcomes Framework (QOF) [20]. The control practices will have the trial software installed, but this will run in a non-active format. There will be no eligible list generated and no screen reminders. The software will record the number of patients eligible for anticoagulation, the number receiving treatment and other secondary study outcomes throughout the trial.

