#### Secondary outcomes

Secondary outcomes include the following:

1. The proportion of patients with CHADS_2_ score ≥2 prescribed anticoagulants. CHADS_2_ is a commonly used scoring system for stroke risk in atrial fibrillation [8].

2. A record of inappropriate care or prescribing related to anticoagulation in patients with AF.

3. The incidence of stroke, transient ischaemic attack (TIA), or other major thromboembolism during the trial, in patients with AF eligible for OAC.

4. The incidence of major haemorrhage during the trial in patients with AF eligible for OAC.

The denominator for the primary outcome will be all of those eligible for OAC therapy at the end of the 6-month trial period. This will include those whose eligibility has arisen since the start of the trial, for instance through reaching the 65- or 75-year age thresholds, or through a new diagnosis of a condition relevant to eligibility. It is important that the size of the denominator population is not influenced by use of the tool, as this could lead to ascertainment bias. We will therefore exclude from the outcome denominator those whose eligibility has arisen during the study purely as a result of improved recognition of diabetes, hypertension, heart failure, or thromboembolic stroke by the AURAS-AF tool, as the control arm will not be influenced by this improved recognition (see ‘Intervention’ section above). This group will be identifiable through the recording of responses to screen prompts. Patients diagnosed with these conditions independently of the tool will not be excluded. Similarly, cases where an ‘Atrial Fibrillation Resolved’ code is applied (effectively removing the patient from the study population) will be retained in the denominator if this decision resulted directly from the use of the AURAS-AF tool in the intervention arm.

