### Data collection

The primary data collection will use the capabilities of EMIS Web. The research team will enter into data sharing agreements with practices allowing us to securely access anonymous outcome data over an N3 NHS (secure) internet connection. Proportions of patients prescribed OACs, and incidence of stroke, TIA, other major thromboembolism and major haemorrhage in the TA249 eligible sample will be collected in this way. We will collect these outcomes at baseline, 3 months into the trial (for the data monitoring committee), at 6 months (at the end of the intervention phase) and after 12 months (see Additional file 1).

We shall additionally ask practices - both intervention and control - to fill in *pro forma* providing further information on strokes, TIAs, other major thromboembolisms and major haemorrhages. The number of these required from each individual practice is expected to be small. These will include information about the anticoagulation status (including international normalised ratio if available) at the time of the event and duration on therapy. The *pro forma* data will help to attribute outcome events to decisions around prescribing and the possible influence of the AURAS-AF software on these decisions. Intervention practices will also be asked to complete *pro forma* providing details of patients’ contact with the practice during the study that is relevant to anticoagulation. This will include responses to the initial invitation to consultation, and reasons behind decisions over therapy where discussions occurred. The main outcome data will be extracted immediately following the intervention phase, including the *pro forma*, with a second extract after a further 6 months. Finally, we ask practices to report any inappropriate care or prescribing in the AF population to the study team within one week of its occurrence.

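### Stroke type, and possibly event dating, could be ascertained differently by arm, because only intervention practices are prompted to clarify strokes in the records that supply the event outcomes

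*Protocol article*

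**What the plan says.** **The prompt.** Under Intervention, "the tool requests clarification over the nature (thromboembolic or haemorrhagic) of past recorded strokes, where non-specific electronic codes" were used. The section adds: "This clarification is obtained by responses to screen prompts and these responses will be collected during the study". The stated reason is that the distinction affects eligibility for anticoagulation.

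**The control arm.** Under Control practices, the software is installed but inactive: "There will be no eligible list generated and no screen reminders".

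**The safeguard.** The Secondary outcomes section recognises ascertainment bias from the tool. It removes from the denominator patients who became eligible purely because the tool improved recognition of certain diagnoses, thromboembolic stroke among them, "as the control arm will not be influenced by this improved recognition". The paragraph is introduced as a definition of the primary outcome denominator.

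**The event outcomes.** Outcome 3 is "The incidence of stroke, transient ischaemic attack (TIA), or other major thromboembolism during the trial, in patients with AF eligible for OAC". Outcome 4 is major haemorrhage in the same population. Under Data collection, "incidence of stroke, TIA, other major thromboembolism and major haemorrhage in the TA249 eligible sample will be collected in this way", meaning by remote extraction from EMIS Web at baseline and at 3, 6 and 12 months. The 3-month extract is for the data monitoring committee. Statistical analyses compares the incidence rates between arms.

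**A second source.** Data collection also asks practices in both arms for a pro forma on each stroke, TIA, other major thromboembolism and major haemorrhage. Its stated role is to add information and to help attribute events to prescribing decisions. It is not named as the source that decides whether an event counts, when it happened or what type it was.

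**The concern.** One arm receives an instrument that sharpens the classification of stroke, and the records in which it operates are the stated source of the stroke and haemorrhage counts. The protocol sees this problem for the denominator and deals with it there, but states no equivalent rule for the numerators.

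Two things could differ by arm with no difference in patients. The first is stroke type: a non-specifically coded stroke may be resolved as thromboembolic or haemorrhagic in an intervention practice and stay unresolved in a control practice. The second is dating: if answering a prompt creates or changes a coded entry, an old stroke could acquire a date inside the trial.

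Outcomes 3 and 4 serve objectives 2 and 3, the short-term effect on thromboembolism and the safety of the tool. An artefact confined to the intervention arm could hide benefit or suggest harm. The data monitoring committee would see the same figures during the trial.

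**Working it through.** The plan gives no figure on this point, so there is none to reproduce. Its sample size calculation concerns prescribing and does not bear on it.

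**Reading the sections together**

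1. The prompt is active in the intervention arm only (Intervention; Control practices).
2. The protocol itself says that recognition of thromboembolic stroke then differs by arm (Secondary outcomes).
3. Events come from the same record system and are compared between arms (Data collection; Statistical analyses).
4. The correction concerns who is in the denominator. It does not say which events count or how they are typed.
5. The prompt concerns past recorded strokes, whereas the outcomes are events during the trial. The two can meet because the tool re-reads the record every 24 hours: a stroke early in the trial with a non-specific code could later be treated as a past stroke. This is plausible but not stated.

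**Stroke type: an illustration on assumptions**

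Assume equal true rates. Let a share f of in-trial strokes be coded non-specifically, all truly thromboembolic, all resolved in the intervention arm, and not counted as thromboembolic in control. The apparent rate ratio (intervention/control) is 1/(1 − f).

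| f (assumed) | Apparent ratio |
|---|---|
| 5% | 1/0.95 = 1.05 |
| 10% | 1/0.90 = 1.11 |
| 20% | 1/0.80 = 1.25 |
| 30% | 1/0.70 = 1.43 |

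The ratio is 1.00 if every stroke code counts as a stroke, or if type is settled in the same way in both arms. The same formula applies to outcome 4, with f as the share of major haemorrhages that are non-specifically coded haemorrhagic strokes.

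For scale, take the plan's 53% and 66% uptake and the upper-limit 67% stroke reduction quoted in the Background. The largest true effect is 1 − (1 − 0.66 × 0.67)/(1 − 0.53 × 0.67) = 1 − 0.558/0.645 = 13.5%. This assumes the full uptake difference throughout follow-up.

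**Dating: why no size can be given**

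Assume 80 eligible patients per practice, 15% with a past stroke, 30% of those non-specifically coded, and 3% to 6% strokes per year untreated. None of these is in the protocol.

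- Prompted past strokes: 80 × 0.15 × 0.30 = 3.6 per practice.
- True strokes in 6 months: 80 × 0.5 × (0.03 to 0.06) × 0.645 = 0.77 to 1.55 per practice.
- 10% misdated: 0.36 extra events, or 0.36/1.55 to 0.36/0.77 = 23% to 47%.
- 10% misdated, with only the 47% not on anticoagulants prompted: 3.6 × 0.47 × 0.10 = 0.17, or 11% to 22%.
- 1% misdated, all prompted: 0.036 extra events, or 2% to 5%.
- No change to the coded record: 0%.

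The answer follows the assumed misdating rate, on which the protocol gives no information.

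**The case against.** The strongest reply is that the protocol describes prompt responses being logged, not stroke codes being rewritten. Where a clinician is to apply a code, as in option 3 of the reminder, the text says so; for stroke clarification it does not. The prompt serves eligibility and looks at past strokes. If outcome 3 means stroke of any type, typing cannot change its total. Both arms complete event pro forma, and an old stroke with a new date would probably be noticed there. Code lists and extraction rules may sit in Additional file 1 or the full protocol, neither of which is shown.

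Most of this stands, and it limits the point. A reader might infer that intervention practices re-enter stroke diagnoses and so create new events, but no passage says so. It is also true that the total of untyped strokes is stable under retyping.

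It does not dispose of the point. If outcome 3 means thromboembolic stroke, as its phrase on other thromboembolism and objective 2 suggest, type decides what counts. If it means any stroke, outcome 4 may still depend on type, because a non-specifically coded haemorrhagic stroke may be recognised as a haemorrhage only where it has been clarified. The pro forma is available in both arms but has only a supporting role. And the matter is not simply left to another document: the article names the record extract as the source of incidence and sets out the safeguard for the primary denominator.

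**Conclusion.** The point holds as a credible, unquantified risk to secondary outcomes 3 and 4 and to the data monitoring committee's figures. It concerns mainly stroke type, and event dating only if prompt responses change the coded record. It rests on three statements in the protocol: prompts in one arm, events drawn from the same records, and a correction that covers the primary denominator.

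Three stronger readings are not supported. The document does not show that events are in fact counted differently by arm. It does not support an inflation of 23% to 47%, which depends on an assumed 10% misdating rate and on prompting every eligible patient. It does not show harm to the primary outcome, which counts prescribing and has its denominator protected against tool-driven recognition. The ratios of 1.05 to 1.43 are likewise conditional, and 1.00 is possible.

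Whether outcome 3 should include haemorrhagic stroke is the sponsor's choice. The fault is only that the wording leaves it open, and with it any overlap with outcome 4. A change is worth making because it is cheap and the outcomes concern safety.

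**What to change.** In Data collection:

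- Use the EMIS Web extract to identify candidate events in both arms.
- Confirm each event from the event pro forma already requested from both arms: onset date within the follow-up window, and stroke type. Have the forms read with arm, and any mention of the software, removed.
- Do not use prompt responses or tool-prompted codes to count or type events. State whether a prompt response changes the coded record.
- Query events without a returned form, and show those still missing in a sensitivity analysis by extracted code.
- State whether the 3-month figures for the data monitoring committee are confirmed in this way or are provisional.

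In Secondary outcomes, state whether stroke in outcome 3 includes haemorrhagic stroke, and report stroke by type so that overlap with outcome 4 is visible.

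The cost is two fields on an existing form, where they are not already present, and some queries; the protocol expects few forms per practice. One limit remains: practices know their arm when they complete the form, so masking protects the reading of it, not its completion.
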